##### Epworth Sleepiness Scale and Pittsburgh Sleep Quality Index

The ESS and the PSQI are both sleep quality questionnaires. The ESS is widely used in the field of sleep medicine as a subjective measure of a patient’s sleepiness. The overall score ranges from 0 to 24. The scale estimates whether the patient is experiencing excessive sleepiness that possibly requires medical attention [87]. The PSQI is a self-reporting questionnaire that assesses sleep quality over a 1-month time interval. The global PSQI score is calculated by adding the 7 component scores, providing an overall score ranging from 0 to 21, where lower scores denote a healthier sleep quality [88].

As determination of the MCID in the sleep quality questionnaires remains controversial, with no consensus on methodology, we will estimate the minimum clinically important improvement in the ESS and PSQI to lie between −2 and −3 for this trial [88-92].

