#### Primary Outcome Measures

The primary outcomes are the differences in changes from baseline to postintervention in hormone release (sAA, cortisol, and melatonin levels in salivary and hair samples) and sleep quality, as measured by the ESS and the PSQI.

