#### Statistics

A linear mixed effect regression model will be applied to compare intervention arms against the control at baseline and stimulated measures for the HPA axis or the retinal–SCN–pineal axis comprising cortisol, melatonin, and sAA [106]. Baseline characteristics of patients from each group will be compared applying independent *t* tests, 2-way repeated-measures ANOVA, and the Fisher exact test. To grade the RP severity (by quantifying clinical features, the ETDRS score, and visual field deviation) and the primary outcomes, we will consider both to be continuous variables and apply a multiple linear regression model. For secondary outcomes, normally distributed variables will be statistically assessed via parametric tests, such as the *t* test or ANOVA, while nonnormal distributed variables will be assessed with nonparametric tests, such as the chi-square test or the Fisher exact test and the Mann–Whitney U test. A chi-square or Fisher test will be performed to compare STAI, PSQI, and ESS scores among groups.

Statistical associations between covariates and outcomes will be evaluated using the appropriate statistical methodology, as previously described. Multivariable linear regression models will be appropriately fitted to continuous data based on the distributions of those data. Multiple logistic regression models will be fitted for all dichotomous outcome variables. Appropriate variable selection methods and model fit statistics will be used to determine the best-fitting model to determine the effects of treatment after adjusting for significant effects of covariates.

Finally, any protocol amendment will be first submitted to the Institutional Review Board for approval. If the amendment changes anything about what is reported

on ClinicalTrials, then the study’s registration on ClinicalTrials will be updated accordingly.

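### The PSQI and ESS scores, both primary outcomes, are assigned a chi-square or Fisher test that does not fit numeric change scores and conflicts with the plan's own linear regression and sample-size basis

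*Protocol article*

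**What the plan says.** - **Outcome.** Primary Outcome Measures: "The primary outcomes are the differences in changes from baseline to postintervention in hormone release" (salivary and hair biomarkers) "and sleep quality, as measured by the ESS and the PSQI". STAI is not listed there.
- **Scales.** The section on the two sleep questionnaires describes the PSQI as "providing an overall score ranging from 0 to 21, where lower scores denote a healthier sleep quality". For the ESS it says "The overall score ranges from 0 to 24". It adds: "we will estimate the minimum clinically important improvement in the ESS and PSQI to lie between −2 and −3 for this trial".
- **Schedule.** Table 3 has ESS, PSQI and STAI at V0 and V4, so every patient should have a baseline and an end-of-intervention score.
- **Test.** Statistics: "A chi-square or Fisher test will be performed to compare STAI, PSQI, and ESS scores among groups". This is the only sentence in that section that names these instruments. The linear mixed model is assigned to cortisol, melatonin and sAA.
- **Competing text.** In a sentence that begins with grading RP severity, the same section says the primary outcomes will be treated as continuous in a multiple linear regression. It also promises multivariable models for treatment effects, and says of them: "Appropriate variable selection methods and model fit statistics will be used to determine the best-fitting model". Covariates and Confounders lists preintervention sleep quality scores among the potential covariates.
- **Size.** Sample Size Calculation gives 48 patients (12 per group), alpha 5%, actual power 80.02% and Cohen d 1.2. It then cites a chosen effect size of 0.6, and 60 patients (15 per group) after a dropout allowance of about 20%.

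**The concern.** Chi-square and Fisher tests compare counts across categories. Applied to PSQI or ESS scores they treat each value as an unordered label, take no account of the V0 score, and return a p-value with no mean difference to set against 2 to 3 points. The outcome is a between-group difference in change, so the named test does not address it unless the scores are first turned into responders. No responder rule is attached to the sentence.

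Two analyses of the same primary scores can be read from one section, and neither is named as primary. The choice between them could then be made after the results are known. The choice also matters for power in a trial with 12 to 15 patients per group.

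**Working it through.** **1. The plan's own figure.** For a two-sided two-sample t test the noncentrality is d·√(n/2) = 1.2·√6 = 2.94 on 22 df. At alpha 0.05 this gives power 80.21%, and the required n is 11.94, rounded up to 12; 12 × 4 = 48. The stated 80.02% is within 0.2 points. (The protocol does not state sidedness; a one-sided test would give 88.5%.) A four-group ANOVA with f=0.5 and N=48 gives 80.3%. Both are comparisons of means. Dropout: 48 / (1 − 0.20) = 60. Separately, 0.6 read as Cohen d does not lead to these numbers: power is 29.0% at n=12 and 35.5% at n=15.

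**2. Does the named test use score order?** Permuting the score columns of a group-by-score table left the chi-square p-value at 0.686 both ways. Order is ignored.

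**3. Power under each reading.** Simulated PSQI-type scores, rounded and limited to 0-21. Assumed, not in the documents: mean 11, SD 3.5, normal before rounding, V0-V4 correlation r of 0.5 or 0.7. There were 2,500 trials per setting (simulation error up to about ±2 points), two groups, two-sided 0.05. On this SD, d=1.2 is 1.2 × 3.5 = 4.2 points and d=0.6 is 0.6 × 3.5 = 2.1 points, near the lower end of the stated important improvement. The responder is a fall of at least 3 points from V0.

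| Power, % | n=12, d=1.2, r=0.5 | n=12, d=1.2, r=0.7 | n=15, d=1.2, r=0.5 | n=15, d=0.6, r=0.5 | n=15, d=0.6, r=0.7 |
|---|---|---|---|---|---|
| Chi-square, raw scores | 3 | 3 | 7 | 2 | 2 |
| Fisher, median split | 50 | 53 | 58 | 14 | 13 |
| Chi-square, median split | 64 | 67 | 70 | 22 | 22 |
| Fisher, responder | 49 | 73 | 56 | 13 | 20 |
| Chi-square, responder | 67 | 86 | 71 | 24 | 37 |
| t test, V4 score | 78 | 80 | 89 | 35 | 35 |
| t test, change | 78 | 94 | 88 | 34 | 54 |
| ANCOVA on V0 | 87 | 96 | 95 | 42 | 59 |

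Repeat runs at n=12, d=1.2, r=0.5 gave about 80% for the t test, up to 90% for ANCOVA, up to 68% for the responder chi-square, and 50-60% for Fisher on a median split (the upper end when scores are not rounded, so there are no ties).

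**4. Why the pattern arises.** The raw-score table is so sparse that chi-square rejects in only 0.5-1.2% of trials under no effect. An exact test on the full score table was not run. ANCOVA shrinks the residual SD by √(1 − r²), so d=1.2 acts like 1.2/0.866 = 1.39 at r=0.5 and 1.2/0.714 = 1.68 at r=0.7. A change score has SD √(2(1 − r)) times the score SD: 1.00 at r=0.5 and 0.775 at r=0.7, where d=1.2 acts like 1.55. This is why the responder tests improve with r.

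**5. Four groups, as the sentence is worded.** With n=15, shifts 0/0.6/0.6/1.2 SD and r=0.5: chi-square on raw scores 10%, chi-square on a median split 54%, ANOVA 78%, ANCOVA 87%.

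**The case against.** The strongest reply is that the chi-square/Fisher sentence does not stand alone. The Statistics section also treats primary outcomes as continuous under linear regression, and preintervention sleep scores are a listed covariate. A reader might infer that the plan has no way to estimate the sleep effect. The documents do not support that, since a baseline-adjusted estimate can be assembled from them. What remains is that the regression sentence is tangled with severity grading, does not name PSQI or ESS, and is not ranked above the sentence that does.

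A second reply is that the authors meant responders. The plan states important differences and provides logistic regression for dichotomous outcomes, so this is plausible. A responder by change uses baseline and does test change. At r=0.7 its chi-square version (85-86%) is not weaker than a t test on V4 scores (about 80%), though it stays below ANCOVA. So the 3% for raw scores should not be taken as the power the trial will have; it belongs to one reading. But the text says scores and ties no threshold to the test.

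Third, 12 per group is the pre-dropout figure. The plan is for 60, and the 5-10% loss expected under Missing Data leaves 54 to 57. The n=15 columns show the same ordering of ANCOVA over the count tests. The trial also calls itself a feasibility RCT, but that does not make the named test fit its outcome.

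Finally, a reader might infer that covariate selection biases the treatment effect, especially as anxiety and insomnia medication are candidates. The protocol gives no timing for those variables and no effect was quantified, so this is a secondary point only. Nor does the point extend to the secondary eye outcomes, for which t tests or ANOVA are named when data are normal.

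**Conclusion.** The sentence is wrong as written. It assigns a test of counts to two numeric primary outcomes defined by change, with no cut-off, and it contradicts the continuous treatment of primary outcomes in the same section and the means-based sample size. That conclusion needs no assumed figures.

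The size of the loss does rest on assumptions (SD 3.5, mean 11, r 0.5 or 0.7) and on the reading. At the plan's own design point it runs from near-total for raw scores to about 10 points below ANCOVA for a responder chi-square at r=0.7. ANCOVA had the highest power in every non-null setting run.

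**What to change.** Replace the sentence. Analyse PSQI and ESS at V4 by one named baseline-adjusted linear model (ANCOVA or an equivalent mixed model) with treatment group and the V0 score as terms, reporting adjusted mean differences with 95% confidence intervals. Treat STAI, which the same sentence covers, in the same way as a non-primary score. Keep chi-square or Fisher only for a secondary responder analysis with one prespecified cut-off.

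For this primary model, list the covariates in advance as baseline values, in place of selection by significance or fit.

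The cost is wording only. The trial has not started, and Table 3 already schedules the V0 and V4 scores.

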#### Covariates and Confounders

Several variables will be measured as potential covariates, including preintervention sleep quality scores, concomitant procedures, medical comorbidities, alcohol use, antianxiety medications or other nonprescribed medications used to help with insomnia and anxiety relief, tobacco use, and nonsteroidal anti-inflammatory drug (NSAID) and others anti-inflammatory drug treatment. In addition, basic demographic information will be obtained.

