### Statistical Analysis

#### Sample Size Calculation

A sample size estimation of 48 patients (n=12, 25%, per group) was calculated for a target power of 80% and considering an α (probability of rejecting a true null hypothesis) of 5% and an actual power of 80.02%. Cohen d was 1.2 [101]. Due to the possible overestimation of the effect size in pilot studies, an effect size of 0.6 (medium-high) was chosen for this study. We calculated a total sample size of 60 participants (a total of 15, 25%, patients per group), adding approximately 20% (3 more patients per group than before) to manage possible dropouts [102-105].

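### The covariates in the adjusted treatment model are to be chosen from the trial's own data, so the nominal 5% error rate is not assured for that analysis

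*Protocol article*

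**What the plan says.** The second paragraph of the Statistics section provides linear regression for continuous data and logistic regression for dichotomous outcomes. It then brings in variable selection methods and states that "model fit statistics will be used to determine the best-fitting model to determine the effects of treatment after adjusting for significant effects of covariates". It gives no selection method, threshold or fixed set of terms.

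The candidates are in the Covariates and Confounders section: "Several variables will be measured as potential covariates, including preintervention sleep quality scores, concomitant procedures, medical comorbidities, alcohol use". That list continues with drugs for anxiety or insomnia, tobacco and anti-inflammatory drugs. Basic demographic data are to be collected as well. The word *including* leaves the list open.

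The error rate is set in the Sample Size Calculation section: "considering an α (probability of rejecting a true null hypothesis) of 5"%.

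The first paragraph of the Statistics section names other treatment comparisons: a linear mixed model of the arms against control for cortisol, melatonin and α-amylase, and chi-square or Fisher tests for STAI, PSQI and ESS. No selection step is attached to these, and the section does not say which analysis is confirmatory.

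**The concern.** The t or F reference distribution for a treatment coefficient belongs to a model fixed before the outcomes were seen. If covariates are kept because they fit these patients well, the residual variance of the chosen model tends to be too small. The treatment test then looks more precise than it is: p-values can be too low and intervals too narrow.

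Two further consequences do not depend on the size of that effect.

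- The outcome's own baseline value, probably the most prognostic variable collected, stays only if it is significant.
- The adjustment set can differ between α-amylase, cortisol, melatonin, ESS and PSQI, so treatment effects would not be adjusted alike across endpoints.

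**Working it through.** **1. The plan's own figure.** The stated inputs are a 5% α, "Cohen d was 1.2", 12 per group and "an actual power of 80.02"%. For a two-sided two-sample t test, the noncentrality is d·√(n/2) = 1.2·√6 = 2.94 on 22 degrees of freedom. The power is 80.2%, which agrees with the stated figure to about 0.2 points. With 20% loss, 48/(1 − 0.20) = 60. The 48 therefore corresponds to a plain two-group test at 5% with no selected covariates. (It follows from 1.2 and not from the 0.6 also stated, which is a separate matter.)

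**2. Number of candidates.** The Covariates and Confounders section lists about 7 items, or 9 if the two drug items are each split, before demographics. I take 7 to 12 as the working range. This is an assumption.

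**3. Simulation under no treatment effect.** There are four randomised arms of n = 12 or 15, K independent N(0,1) covariates and normal outcomes. Arm is forced in, and covariates are removed backwards, by p<0.05 or by AIC. The test is t = estimate/SE for the combined arm against control at 0.05. With k covariates kept, the residual degrees of freedom are 4n − 4 − k. Type I error is rejections divided by runs. With 3,000 runs the Monte Carlo standard error is √(0.05·0.95/3000) = 0.4 points.

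Results for K = 10, in percent:

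| Covariates | n per arm | All kept, no selection | p<0.05, arm in model | AIC, arm in model | Backward p<0.05, arm ignored | Univariate screen, arm ignored |
|---|---|---|---|---|---|---|
| All noise | 12 | 4.9 | 6.5 | 7.9 | 5.2 | 5.2 |
| All noise | 15 | 5.3 | 6.6 | 8.2 | 5.7 | 5.5 |
| Three prognostic | 12 | 4.9 | 7.0 | 7.0 | 4.8 | 5.1 |
| Three prognostic | 15 | 5.3 | 7.4 | 7.4 | 5.5 | 5.4 |
| All weakly prognostic | 12 | 4.9 | 9.0 | 8.2 | 4.8 | 5.1 |

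In the same runs with arm in the model, the F test across all arms gave 8.1–12.0% at N = 48 and 6.5–9.0% at N = 60.

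**4. Varying the candidate count and the number of arms.** These are separate runs with noise covariates only (2,500 per setting, standard error about 0.4 points) and arm in the model. Each cell shows 9 / 12 candidates, in percent:

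| Fit | n per arm | p<0.05 | AIC |
|---|---|---|---|
| Four arms | 12 | 7.0 / 6.3 | 7.4 / 8.7 |
| Four arms | 15 | 5.6 / 6.8 | 7.2 / 8.4 |
| Two arms only | 12 | 8.7 / 11.1 | 11.2 / 16.8 |
| Two arms only | 15 | 6.9 / 8.6 | 9.1 / 12.7 |

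Four-arm fits with 7 to 9 candidates and p<0.05 gave 5.1–6.2% at n = 14–15 and 6.1–6.6% at n = 12.

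**5. Why the rule matters.** With arm in the model, selection favours covariates that shrink the within-arm residual. Over two- and four-arm settings with 9 to 15 candidates, the mean residual variance of the selected model was 0.57–0.96 against a true value of 1. If selection ignores arm, randomised labels remain independent of both the outcome and the chosen covariates under the null, and the test stays close to 5%.

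**The case against.** **The sentence may be supplementary.** Its paragraph opens with associations between covariates and outcomes, while the primary hormone and sleep outcomes have their own named analyses. A reader might infer that all the trial's treatment tests come from the selected model. The document does not say so, and that part of the objection stands. Still, the sentence states that treatment effects are determined from this model, and it is not limited to secondary or exploratory outcomes.

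**The 5% rate may hold.** A reader might infer that it fails, or doubles. It is kept when covariates are chosen without regard to arm, and the protocol does not exclude that. This stands: 5% is not assured, but it is not shown to fail. Blinding the statistician does not settle the matter, because a coded group term can sit in the model during selection.

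**The large figures need unstated choices.** Two-arm refits and AIC are not in the protocol, nor is a list of 20 candidates (9.6–15.4% for the pairwise test at N = 48). Reference to significant covariates points to p-value retention. Table 2 excludes patients on anti-inflammatory or psychotropic drugs, so two listed items should vary little at baseline. The Missing Data section expects 5–10% dropout, so 12 per arm is the pessimistic end. All this stands and limits the size.

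**Baseline is already handled.** The primary outcomes are changes from baseline, and the mixed model covers baseline measures. That softens the point for the named analyses. It does not secure baseline adjustment in the regression governed by this sentence.

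**An analysis plan could settle it.** It could name the algorithm. It could not fix the covariates for this analysis without contradicting the sentence.

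**Conclusion.** The point holds for the adjusted regression: as worded, it lets the data choose the adjustment set and then reports treatment effects as if that set had been fixed. For a single arm-versus-control test at nominal 5%, a realistic size is about 5–9% in four-arm fits with arm in the model during selection. It is about 7–17% if models are refitted on pairs of arms, and near 5% if selection ignores arm. These figures assume randomised arms, independent normal covariates, 7 to 12 candidates and backward elimination. The protocol states neither the candidate count nor the selection method, so the size is illustrative. The possible loss of the baseline value and the uneven adjustment across endpoints follow from the wording alone. The documents do not support the claim that the primary analyses as a whole have lost their error control. It should be corrected before the trial starts.

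**What to change.** Replace the selection sentence with a fixed covariate set for every adjusted treatment comparison, linear or logistic: arm and the outcome's own V0 value where measured, with baseline RP severity grade as an optional third term. Keep all terms whatever their p-values, with no data-driven selection. Use the same terms if the hormone mixed model is adjusted. Label the covariate–outcome association models exploratory and read no treatment p-values from them.

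The cost is one paragraph of wording. Table 3 already schedules the saliva, hair, STAI, ESS and PSQI measurements at V0, and severity is graded for eligibility, so no data or patients are added. The small downside is that a prognostic covariate outside the set is not used.

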#### Modification/Discontinuation

If patients experience unbearable side effects related to melatonin, they must leave their intervention group. If they wish, they can continue participating in the study as part of the SWL group being evaluated over the 4-week follow-up period. To reflect these changes at the end of the study, an intention-to-treat analysis will be conducted.

#### Missing Data

Dropouts and missing facts are known as missing data. A dropout rate of 5%-10% is expected based on recent OM clinical trials [99,107]. An intention-to-treat analysis, regardless of the treatment administered, will be carried out for every primary and secondary endpoint. A preprotocol analysis will also be conducted with those who complete the trial, since secondary outcomes could be more affected by uncensored withdrawals. Both analyses must be favorable for the intervention to be considered better than standard. To deal with missing data, imputation techniques will be applied.

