##### Ancillary Tests

Visual field impairment (VFI) will be assessed using a Humphrey 750i visual field analyzer (Carl Zeiss) and the central 30-2 SITA fast strategy protocol. Only tests that met the criteria (low [<20%], false positive, false negative, and fixation loss parameters) were evaluated [84].

Optical coherence tomography (OCT) images, assessing the central retinal thickness (CRT), macular ganglion cell–inner plexiform layer (GCIPL) thickness, and retinal nerve fiber layer (RNFL), will be performed using Cirrus HD-OCT 5000 with AngioPlex OCT-A (Carl Zeiss Meditec V.10.0) and cube scans. Only images with a signal strength of >6 with no movement artifact will be included in the study.

Two consecutive optical coherence tomography angiography (OCTA) images will be obtained by a single skilled examiner. A foveal centered scan area of a 3×3 mm^2^ pattern will be used, and all scans will be analyzed using en face OCTA images generated automatically with the optical coherence tomography microangiography (OMAG) algorithm in Angioplex software (ZEISS). The foveal avascular zone (FAZ) area will be manually outlined and expressed as square millimeters.

The vascular density (VD) will be measured automatically by the software, which will quantify the VD of a local region of tissue according to the ETDRS subfields. We will analyze the VD of each ETDRS sector, the inner ring, and the full area in 3×3 mm^2^ rings and exclude OCTA images with a signal strength of <7 [12].

The axial length will be calculated using an IOLMaster 500 optical biometer (Carl Zeiss Meditec) to be used as a correcting variable in the analysis, if necessary.

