#### Secondary Outcome Measures

Secondary outcome measures include any clinical macular changes or retinal function measured with the ETDRS scale, CSV-1000 chart, and ancillary tests, such as the VFI, OCT, and OCTA. In addition, several patient-reported variables, such as self-recorded sleep diaries, perceived stress, and functional status will be recorded.

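### The rule for calling the intervention better is not limited to the primary outcomes, and the secondary tests beneath it are loosely chosen, so a false secondary benefit is several times more likely than 5%

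*Protocol article*

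**What the plan says.** **Success rule.** The Missing Data section says "An intention-to-treat analysis, regardless of the treatment administered, will be carried out for every primary and secondary endpoint". It adds an analysis of those who complete the trial, justified by the effect of withdrawals on the secondary outcomes. It then concludes: "Both analyses must be favorable for the intervention to be considered better than standard". The word favorable is not defined, and the rule does not say which endpoints it governs.

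**Tests.** The Statistics section says: "For secondary outcomes, normally distributed variables will be statistically assessed via parametric tests", naming the t test or ANOVA. Non-normal variables get chi-square, Fisher or Mann-Whitney tests. STAI, PSQI and ESS scores are compared among groups by chi-square or Fisher test.

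**Secondary set.** The list is open: "Secondary outcome measures include any clinical macular changes or retinal function measured with the ETDRS scale", then the contrast chart, visual field, OCT, OCTA and several patient-reported variables. The Ancillary Tests section widens the OCTA part: "We will analyze the VD of each ETDRS sector, the inner ring, and the full area". Table 3 schedules clinical assessments at V0, V4 and 6 months.

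**Significance level.** The only alpha in the article is in the Sample Size Calculation.

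**The concern.** The rule directly follows a sentence covering primary and secondary endpoints alike, and the completer analysis it depends on is justified by the secondaries. Read plainly, secondary results can count towards the claim of superiority. The article's Conclusion looks for benefit in disease progression, yet every retinal measure is secondary. A retinal difference arising by chance after 30 days of treatment in about 15 patients per arm could therefore be presented as serving a stated aim.

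The choice of test makes this worse. For a continuous secondary that is not normal, the only rank test named compares two groups, and the trial has four. For a normal one, the choice between t tests and ANOVA is left open. With small arms, whether a variable counts as normal will often be uncertain, so the test may depend on the data. Nothing in that choice uses the outcome's own V0 value, although the clinical measures are taken at V0.

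**Working it through.** **1. The plan's own figure.** The Sample Size Calculation says: "A sample size estimation of 48 patients (n=12, 25%, per group) was calculated for a target power of 80"%, with "Cohen d was 1.2". A two-sample t test at two-sided 5% with d = 1.2 needs n = 11.94, so 12 per group, and 12 per group gives power 80.2% (stated: 80.02%). Allowing 20% for dropout, 12/(1 − 0.20) = 15 per group. So the 5% in the article fits one comparison of two groups on one outcome. It does not describe the secondary set.

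**2. Inputs.**
- From the article: four arms, three of them compared with one control; 15 per arm.
- Assumed: each secondary is tested at two-sided 5%, so a false benefit in one comparison has probability 2.5%.
- Assumed: 2 of 15 per arm are missing from the completer set. The article expects 5%-10% dropout (0.75 to 1.5 per arm) and allows for 3 per arm. The ITT set is treated as complete.
- Assumed: 14 ophthalmic measures at one visit. Seven are acuity, contrast, visual field, central thickness, GCIPL, RNFL and FAZ. Seven are vessel-density values (taken as five sectors, the inner ring and the full area). The range 8 to 20 brackets this count.
- Assumed: equal correlation between measures, from 0 to 0.8.
- Excluded: diary comparisons with control during the intervention. Table 1 and the No Intervention section show that controls keep no diary then.

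**3. Simple bounds for m independent measures.**
- One four-group test per measure, any difference: 1 − 0.95^m = 34%, 51% and 64% for m = 8, 14 and 20.
- Any of three benefits over control, ignoring the shared control: 1 − 0.975^(3m) = 46%, 65% and 78%.

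**4. Simulation of the rule as worded.** There is no true effect and the control arm is shared. A hit is a benefit over control that is significant in both the ITT and the completer set (6,000 runs per cell, standard error at most about 0.6 points).

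| Measures | corr. 0 | 0.3 | 0.5 | 0.8 |
|---|---|---|---|---|
| 8 | 29% | 24% | 20% | 13% |
| 14 | 46% | 35% | 27% | 16% |
| 20 | 59% | 44% | 33% | 19% |

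Repeat runs for 14 measures at correlation 0.5 gave 27% to 29%; 28% is used here. With one measure only, the figure is about 4%, so the excess comes from the number of measures.

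**5. If ANOVA is used instead.** One four-group test on each of 14 measures gives about 52% at correlation 0 and 22% at 0.8. This counts any difference, in either direction, in the ITT set alone. Choosing ANOVA does not by itself bring the rate near 5%.

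**The case against.** The case against a stronger reading is good, and most of it stands.

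- **A chance benefit is more likely than not.** A reader might infer this from counting every significant difference from control: about 77% for 20 measures at correlation 0.5. That figure includes harms and ignores the requirement that both analyses agree. If four of the 20 are diary measures, it also counts 4 × 3 = 12 of 60 comparisons for which controls have no data. Under the rule as worded, one half is passed only with about 20 uncorrelated measures, or with 14 uncorrelated measures counted at both visits. Neither is plausible for neighbouring sectors and layers of the same eyes.
- **Only two-group tests are planned.** The article also names ANOVA, and the questionnaires have an among-groups test.
- **Each secondary is tested at 5%.** The article sets no level for secondaries; 5% is carried over here as an assumption.
- **One secondary result is enough for success.** The rule does not say so. It is an agreement requirement between two analyses, and its scope is unclear.
- **Missing multiplicity detail.** An adjustment or an exploratory label may stand in an analysis plan or full protocol not shown. Unadjusted secondaries are common, and the abstract calls the trial a feasibility study. The absence of an adjustment is not the point made here.
- **Covariate adjustment.** The Statistics section does plan regression models with covariates. Those are chosen by variable selection, and the covariate list names preintervention sleep quality scores, not the V0 value of each secondary.

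What remains is text the article does state: a success rule with no limit to the primary outcomes, and a loose choice of test for the secondaries.

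**Conclusion.** The point holds in this limited form. The success rule is worded over primary and secondary endpoints without distinction, and the named tests leave the secondary comparisons open. If secondaries are tested at 5%, the chance of at least one false benefit over control that passes both analyses is about 13% to 59%, with 28% as a central value. Against 5%, that is 2.6 to 11.8 times (13/5 and 59/5), and 5.6 times at the central value. These figures rest on the assumed level, the assumed number of measures (8 to 20), one visit, equal correlations of 0 to 0.8, and 2 of 15 per arm missing from the completer set. Counting the 6-month visit as well would raise them. The documents do not support saying that a false benefit is more likely than not.

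**What to change.** 1. In Missing Data, state that the conclusion that the intervention is better than standard rests on the primary outcomes only, and say what counts as favorable.
2. State there that secondary results are supportive or exploratory, reported as estimates with 95% confidence intervals.
3. In Statistics, replace the normality-dependent choice among t test, ANOVA and Mann-Whitney for continuous secondaries. Use one four-arm model per outcome, adjusted for its V0 value (rank-based where needed), and take the arm-versus-control contrasts from that model.
4. Optionally, name one vessel-density summary, such as the full area, as the listed secondary and treat the sectors as descriptive.

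The trial has not started and V0 measurements are already scheduled, so this is a change of wording with no new data. The cost is that a significant secondary result alone can no longer support a claim of benefit.
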